### Sample Size

Sample size estimation was performed using G*Power software (version 3.1.9.7; Heinrich Heine University) [48,49]. The calculation was based on the primary outcomes of functional capacity and fall risk, assessed by the 6MWT and the TUGT, respectively. An effect size of 0.56 was adopted based on the findings of Espejo-Antúnez et al [50], who evaluated the effects of a 12-week exercise intervention on functional capacity and fall-related outcomes in older adults. Assuming a 2-group parallel RCT design, a statistical power of 95%, and a significance level of 5% (*α*=.05), the minimum required sample size was estimated at 35 participants per group. Therefore, the study was designed to include 70 participants, with 35 allocated to each group. Because recruitment will be conducted among community-dwelling older adults regularly attending activities at the CONVIVER Community Center, and eligibility will depend on screening procedures, the final sample will be obtained through convenience sampling. Recruitment feasibility was considered during the planning phase to ensure attainment of the target sample size.

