### Statistical Analysis

For the statistical analysis, data normality will be assessed using the Shapiro-Wilk test and Q-Q plots. Descriptive statistics will be performed to characterize the sample. Categorical variables will be presented as absolute and relative frequencies, whereas continuous variables will be expressed as means and SDs or medians and IQRs, in addition to graphical representations. Changes in mean values over time will be represented by delta values (Δ).

The primary analytical model for the 2 primary outcomes (6MWT and TUGT) will be an analysis of covariance, comparing postintervention values between groups while adjusting for the corresponding baseline values. Preintervention and postintervention comparisons will be conducted using the 2-tailed paired Student *t* test for normally distributed variables or the Wilcoxon signed-rank test for nonnormally distributed variables. Between-group differences will be analyzed using the independent Student *t* test for normally distributed variables and the Mann-Whitney *U* test for nonparametric variables.

Effect sizes will be calculated using eta squared (η²) and Cohen *d* and interpreted as small (0.2), medium (0.5), or large (0.8). All losses to follow-up and their respective treatment durations will be recorded for intention-to-treat analysis. All participants will be reassessed after the 12-week intervention period whenever possible. Missing data will initially be explored to determine the pattern and mechanism of missingness. When appropriate, missing outcome data will be handled using multiple imputation methods based on chained equations. Sensitivity analyses will be conducted to compare the results obtained from complete-case analyses and imputed datasets in order to evaluate the robustness and consistency of the findings. In addition, per-protocol analyses will be performed as secondary sensitivity analyses to assess the influence of adherence to the intervention on study outcomes. A significance level of *P*<.05 will be adopted for all statistical tests. Statistical analyses will be performed using the SPSS, version 25.0 (IBM Corp) [51], and graphs will be generated using R software (R Foundation for Statistical Computing) [52].

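### Two primary outcomes are each tested at an unadjusted .05 with no statement of whether one or both must succeed; if either suffices, the false-positive risk is about 8-10%, not 5%

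*Protocol article*

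**What the plan says.** The Statistical Analysis section of the protocol article names the deciding model: "The primary analytical model for the 2 primary outcomes (6MWT and TUGT) will be an analysis of covariance", with the baseline value as covariate. Two further kinds of test follow. For change within each arm: "Preintervention and postintervention comparisons will be conducted using the 2-tailed paired Student *t* test", with a Wilcoxon alternative. For the comparison of arms: "Between-group differences will be analyzed using the independent Student *t* test for normally distributed variables", with Mann-Whitney otherwise. The section closes its list of methods with one threshold for everything: "A significance level of *P*<.05 will be adopted for all statistical tests".

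The Sample Size section uses both outcomes together: "The calculation was based on the primary outcomes of functional capacity and fall risk". It takes one effect size ("An effect size of 0.56 was adopted") and one pair of error rates ("a statistical power of 95%, and a significance level of 5" percent), and concludes that "the minimum required sample size was estimated at 35 participants per group".

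No section gives a hierarchy of the two outcomes, a division of alpha, or a statement that one or both must be significant.

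**The concern.** With two primary outcomes, the error rate of the trial's main claim depends on how their results are combined. If a significant result on either the 6MWT or the TUGT would be reported as showing that the programme works, there are two chances of a false positive, and 5% per test does not give 5% for the claim. If both are needed, alpha is safe but power is lower than for one outcome. The article states 5% and 95% without saying which claim they describe, and its limitations text says that the trial is adequately powered for its primary outcomes. If the rule is left open until the data are in, it can be chosen to suit the result.

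The t test/Mann-Whitney sentence adds a smaller ambiguity. It is neither restricted to other variables nor labelled supportive, whereas the per-protocol analyses in the same section are explicitly labelled as sensitivity analyses. Under Assessment Procedures, the 6MWT and TUGT are the only efficacy outcomes measured again at 12 weeks. The post-intervention IPAQ serves only to monitor contamination (Physical Activity Status). The natural reading is therefore that the sentence yields a second between-group P value on the primary outcomes.

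**Working it through.** **Inputs from the article:** two primary outcomes, ANCOVA for each, .05 per test, 35 per arm, 1:1 allocation, effect size 0.56, power 95%.

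**Assumed, because the article does not give them:** two-sided between-group tests; 0.56 read as a standardised mean difference d, equal for both outcomes; between-outcome correlation 0 to 0.8; baseline-post correlation 0.5 to 0.8.

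**1. The plan's own figure.** A two-sided two-group t test with d=0.56, alpha .05 and 95% power needs 84 per arm (83 by the normal approximation). At 35 per arm its power is 64%. The stated 35 per group is therefore not reproduced by this calculation. ANCOVA scales the SD by √(1−r²), where r is the baseline-post correlation. Power at 35 per arm is then Φ(0.56·√(35/2)/√(1−r²) − 1.96):
- r=0.5: Φ(2.343/0.866 − 1.96) = Φ(0.745) = 77%
- r=0.6: Φ(2.343/0.800 − 1.96) = Φ(0.968) = 83%
- r=0.7: Φ(2.343/0.714 − 1.96) = Φ(1.320) = 91%

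About 35 per arm is reached only with r near 0.76. That is a separate point. It matters here because the cost of any multiplicity rule depends on r.

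**2. False-positive risk if either outcome suffices.** For independent outcomes: 1 − (1 − 0.05)² = 1 − 0.9025 = 9.75%. For correlated test statistics: 1 − P(|Z₁|<1.96 and |Z₂|<1.96), from the bivariate normal distribution.

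| Correlation of the two tests | At least one P<.05 |
|---|---|
| 0 | 9.75% |
| 0.5 | 9.1% |
| 0.7 | 8.35% |
| 0.8 | 7.8% |

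A simulation of 40,000 null trials with 35 per arm and ANCOVA on each outcome gave 9.5-9.7% at correlation 0 and 7.8-9.3% at 0.5-0.8. Testing each outcome at .025 brought it to 4.1-4.9%.

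**3. False-positive risk if both are required.** At most 5%, reached when one outcome truly responds and the other does not. If neither responds and they are independent, it is 0.05 × 0.05 = 0.25%.

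**4. Chance of success under each rule** (simulated ANCOVA, 35 per arm, d=0.56 on both outcomes, between-outcome correlation 0.7):

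| Baseline-post r | Either at .05, unadjusted | At least one, Holm | Both at .05 |
|---|---|---|---|
| 0.5 | 86% | 77% | 65% |
| 0.6 | 90% | 83% | 73% |
| 0.7 | 95% | 91% | 84% |

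The rule alone moves the chance of success by 11 points at r=0.7 (95 − 84) and by 21 points at r=0.5 (86 − 65).

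**The case against.** The strongest reply is that the article already ranks its tests. ANCOVA is named the primary model for both outcomes, so within each outcome it is clear which P value decides. That stands, and it rules out several stronger readings.

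- A reader might infer that nothing says whether ANCOVA or the t test decides. The text does say so. What is missing is the rule across the two outcomes.
- A reader might count the t tests as further chances of success, which would raise the risk to about 11-17% on post values or 10-14% on change scores. Those figures need the t test to be decisive, which the naming of ANCOVA contradicts.
- A reader might infer that Mann-Whitney replaces ANCOVA when the TUGT is skewed. No sentence says so. It would lose the baseline adjustment, but the replacement is inference.
- With a true d of 0.56 and baseline-post correlation 0.6-0.8, ANCOVA and the t test disagree on significance in about 22-34% of trials, which looks like room to pick the better result. Almost all of that is ANCOVA significant and the t test not. The t test alone is significant in only about 0.3-2.5% of trials.

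It can also be said that multiplicity rules commonly belong in an analysis plan, which is not shown. That would hold if the article were silent. It is not: it fixes .05 for every test and uses a single 5% for both outcomes in the sample size.

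Finally, the inflation is conditional, since requiring both outcomes removes it. That is correct, but the article does not say that both are required.

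**Conclusion.** The point holds for the rule across outcomes. Followed as written, a claim resting on either outcome carries a false-positive risk of at most 9.75%, and about 8-9% at assumed between-outcome correlations of 0.5-0.8. It would be too strong to say that the risk is simply double the stated 5%: that is the upper bound for the two ANCOVAs, it needs independent outcomes, which is unlikely for two walking-based tests, and it needs an either-outcome rule. Under a both-outcomes rule there is no inflation, and the issue becomes whether 95% power holds jointly.

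The t test/Mann-Whitney sentence is a real but lesser ambiguity of wording. The within-arm tests do not address the randomised comparison, although the article does not present them as if they did.

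This should be fixed, but it does not undermine the design: the primary model is prespecified and only the combining rule and some labels are missing.

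**What to change.** Before recruitment starts, make three changes in Statistical Analysis.

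1. State one rule: either Holm across the two ANCOVA P values, so that either outcome can support a claim, or both outcomes required at two-sided .05. Say in Sample Size which claim the 95% power refers to.
2. State that ANCOVA is the only deciding between-group test for the 6MWT and TUGT. Label the t test/Mann-Whitney comparisons and the within-group tests as supportive or descriptive.
3. If TUGT residuals are skewed, keep the baseline adjustment, for example by ANCOVA on log-TUGT.

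The change is to text only. The price in power is in the last table of the working. Relative to an unadjusted either-outcome rule, Holm costs 9, 7 or 4 percentage points at baseline-post correlations of 0.5, 0.6 or 0.7 (86 − 77, 90 − 83, 95 − 91). Requiring both costs 21, 17 or 11 points (86 − 65, 90 − 73, 95 − 84). These costs rest on the assumed correlations and on d=0.56 for both outcomes, so the authors should state their own assumed baseline-post correlation when they choose.

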### Safety Assessment and Withdrawal

Participant safety will be monitored throughout the intervention period by the research team and supervising physiotherapists. Any AEs potentially associated with the exercise sessions or assessment procedures, including dizziness, pain, excessive fatigue, musculoskeletal discomfort, falls, cardiovascular symptoms, or any other clinical complaints, will be immediately documented and evaluated.

If a participant develops any AE or clinical instability during the intervention period, exercise participation will be temporarily interrupted, and the participant will be closely monitored by the research team. When necessary, the participant will be referred for medical evaluation before resuming study activities. In cases where symptoms persist, recur after reintroduction of the intervention, or compromise participant safety, the participant may be withdrawn from the study after clinical assessment by the investigators. All AEs and safety-related occurrences will be systematically recorded in standardized monitoring forms throughout the trial period.

Participants will be free to discontinue their participation at any moment and for any reason, including the option to request the removal of their data from the study. Individuals will be considered withdrawn if they formally request to leave the trial or are lost to follow-up. Participants allocated to the intervention group will be classified as withdrawn if they discontinue participation in the supervised exercise program. Participants allocated to the control group will be classified as withdrawn if they discontinue participation in the educational workshops before the completion of the study.

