### Participants

Participants will consist of older adults who regularly attend activities offered by the CONVIVER Community Center for Older Adults in Rio Verde, Goiás, Brazil. The CONVIVER Center is a publicly funded community facility coordinated by the municipal government that provides social, educational, recreational, and health-promotion activities for independently living older adults from the local community.

Individuals who express interest in participating will undergo eligibility screening and baseline assessments after signing the written informed consent form. During the screening phase of the study, frailty status will be assessed to determine the participants’ eligibility.

Inclusion criteria will include (1) age of 60 years or older; (2) living independently in the community; (3) regular participation in activities offered by the CONVIVER Community Center; (4) classification as prefrail or frail according to the Edmonton Frailty Scale (EFS); (5) preserved cognitive function sufficient to understand the study procedures, as assessed using the Mini-Mental State Examination (MMSE); and (6) clinical ability to participate safely in supervised physical exercise activities.

Exclusion criteria will consist of (1) acute or unstable cardiovascular conditions; (2) severe neurological, orthopedic, or musculoskeletal impairments limiting safe exercise performance; (3) severe visual, auditory, or communication impairments compromising assessment procedures; (4) recent hospitalization or clinical instability within the previous 3 months; (5) inability to complete the assessment procedures; and (6) refusal to participate or withdrawal of informed consent at any stage of the study.

Frailty status will be determined using the EFS. Participants scoring between 5 and 6 points will be classified as prefrail, whereas those scoring 7 points or higher will be classified as frail. Individuals scoring between 0 and 4 points, indicating the absence of frailty, will not be eligible for participation in the study [25,26]. Participants attending fewer than 75% of intervention sessions will be considered nonadherent for per-protocol analyses but will remain eligible for intention-to-treat analyses whenever possible.

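### Stopping the sessions counts as withdrawal in either arm, which conflicts with the intention-to-treat and reassess-everyone statements and puts week-12 outcomes at risk

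*Protocol article*

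**What the plan says.** Two sets of statements in the protocol article bear on a participant who stops attending.

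**Withdrawal and exclusion.** Safety Assessment and Withdrawal first defines the status by departure from the trial: "Individuals will be considered withdrawn if they formally request to leave the trial or are lost to follow-up". It then extends the same status to stopping the allocated activity. For the exercise arm: "Participants allocated to the intervention group will be classified as withdrawn if they discontinue participation in the supervised exercise program". For the control arm: "Participants allocated to the control group will be classified as withdrawn if they discontinue participation in the educational workshops before the completion of the study". After persistent or recurrent symptoms, "the participant may be withdrawn from the study after clinical assessment by the investigators"; the wording is withdrawal from the study, not only from exercise. The exclusion criteria under Participants include "refusal to participate or withdrawal of informed consent at any stage of the study".

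**Follow-up and analysis.** Under Participants, those attending fewer than 75% of intervention sessions are nonadherent for per-protocol purposes but "will remain eligible for intention-to-treat analyses whenever possible". Statistical Analysis states: "All participants will be reassessed after the 12-week intervention period whenever possible". It plans chained-equation multiple imputation when appropriate, and sensitivity analyses that "compare the results obtained from complete-case analyses and imputed datasets".

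**The concern.** Stopping treatment and leaving follow-up are different events. An intention-to-treat analysis depends on keeping them apart, because someone who stops the sessions can still be measured and counted in the group to which they were randomised. Here one word covers both events, and nothing says that a person withdrawn for stopping sessions is still invited to the week-12 tests.

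The word will be applied by the people running the sessions and visits, before any analyst sees the data. If they read it in its ordinary sense, the 6-Minute Walk Test (6MWT) and Timed Up and Go Test (TUGT) at week 12 may not be done for that person, and an outcome not collected then cannot be recovered later. The analysis would drift from all randomised participants towards those who kept attending. The sample size leaves no slack: the calculated minimum of 35 per group is also the number to be randomised.

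**Working it through.** **Step 1: set the rules side by side.** The programme has 24 sessions (Intervention Group), so the 75% threshold is 0.75 × 24 = 18 sessions.

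| Exercise participant who | Attendance | Participants section | Safety Assessment and Withdrawal |
|---|---|---|---|
| stops for good after session 10 | 10/24 = 42% | nonadherent, kept for intention-to-treat | withdrawn |
| stops for good after session 20 | 20/24 = 83% | meets the per-protocol threshold | withdrawn |

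Each person falls under two rules. Statistical Analysis would reassess both people where possible, but no sentence states whether the withdrawn status overrides that.

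**Step 2: what would follow if those who stop were not measured.** The protocol gives no stopping rate, so there is no figure of its own to reproduce on this point. The one document input is the planning effect size of 0.56 (Sample Size), taken here as a standardised mean difference in those who continue. The assumptions are a stopping fraction s of 10% to 30% in the exercise arm and no benefit in those who stop.

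- Intention-to-treat effect = (1 − s) × 0.56
- Completer effect = 0.56
- Ratio = 1/(1 − s)

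| s | Intention-to-treat effect | Completer effect | Ratio |
|---|---|---|---|
| 10% | 0.90 × 0.56 = 0.50 | 0.56 | 1.11 |
| 20% | 0.80 × 0.56 = 0.45 | 0.56 | 1.25 |
| 30% | 0.70 × 0.56 = 0.39 | 0.56 | 1.43 |

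**Step 3: the role of the control arm.** The rule applies to both arms. Let those who stop have an untreated outcome w SD worse than those who continue. Write s_E and s_C for the stopping fractions in the exercise and control arms, with the same w in each. The completer contrast is then 0.56 + s_E·w − s_C·w.

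- Stopping in exercise only, s_E = 20%, w = 0.5: 0.56 + 0.10 = 0.66, and 0.66/0.448 = 1.47.
- Stopping in exercise only, s_E = 30%, w = 0.5: 0.56 + 0.15 = 0.71, and 0.71/0.392 = 1.81.
- Equal stopping in both arms: the w terms cancel, and the ratios return to 1.25 and 1.43.
- s_E = 10%, s_C = 30%, w = 0.5: 0.56 + 0.05 − 0.15 = 0.46, against an intention-to-treat effect of 0.504. The ratio is 0.91, so the completer estimate is too small.

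Neither size nor direction is therefore fixed by anything in the document.

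**Step 4: precision.** Losing 10%, 20% or 30% of 35 leaves about 32, 28 or 24 per group. For a two-sided unadjusted t test at 0.56, power is 64% with 35 per group and falls to 60%, 54% and 48%. Baseline adjustment would raise all four values by an amount that depends on a correlation the protocol does not give. (The 64% is below the stated 95%. That is a separate question about the sample size, and this point does not rest on it.)

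**The case against.** The strongest reply is that the withdrawal paragraph only classifies. It does not say that withdrawn people go unmeasured or leave the analysis. The sections that do govern assessment and analysis say that everyone is reassessed where possible and that low attenders stay in intention-to-treat. Most people who stop early will fall below 75% and so already have a stated analysis rule. This stands. A reader might infer that the plan discards the outcomes of those who stop, but the text supports only a risk of that.

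A reader might also infer that the rule must favour exercise, perhaps by 47% or about 80%. Those figures need stopping in the exercise arm alone and a prognosis 0.5 SD worse. The rule covers both arms, and with equal stopping and equal prognosis the figures fall to 25% and 43%. The baseline-adjusted primary analysis would also absorb any part of the deficit already visible at baseline.

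The exclusion criterion about inability to complete assessments reads naturally as a screening criterion, so it is not counted here. The wording on consent withdrawn at any stage does reach past randomisation. It is true that nobody can be reassessed after withdrawing consent, but that is a reason for missing data and not an eligibility criterion.

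Finally, the imputation model and any analysis that departs from missing at random are commonly left to the analysis plan, so their absence is not a fault. Attendance, adverse events and baseline measures could also inform the imputation.

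What remains is the unresolved conflict. The phrase about reassessing whenever possible does not settle it, because someone already labelled withdrawn can be taken as someone for whom reassessment is no longer possible.

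**Conclusion.** The point holds as a conflict between stated rules. Stopping sessions or workshops carries the same status as leaving the trial, and the exclusion criteria extend past randomisation. Both sit against the commitments to intention-to-treat and to reassessing everyone, and no sentence ranks them. The consequence is a risk that week-12 outcomes of people who stop are not collected.

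If that happened, the completer effect would exceed the intention-to-treat effect by about 11% to 43%. This assumes 10% to 30% stopping, no benefit in those who stop, no reassessment of any of them, and no net prognostic difference between the arms from stopping. Other patterns across the two arms give larger, smaller or reversed differences. If those who stop are in fact reassessed, this bias does not arise. The wording should be reconciled before the first participant is randomised; the protocol states that recruitment had not started at submission.

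**What to change.** Reconcile Participants, Statistical Analysis, and Safety Assessment and Withdrawal as follows:

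1. Define two states for both arms. *Discontinued sessions*: no longer attending the exercise or workshops, still invited to the planned 12-week 6MWT and TUGT, and analysed as randomised. *Withdrew consent for follow-up*: no further assessment. Record loss to follow-up as its own reason for a missing outcome.
2. Limit the exclusion criteria to the period before randomisation, and move later withdrawal of consent to the second state above.
3. State that the primary ANCOVA includes all randomised participants in their allocated group.

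A delta-adjusted sensitivity analysis is an optional low-cost addition, because complete-case and standard multiple-imputation analyses both generally rely on assumptions of the missing-at-random type.

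The cost is a few sentences of protocol text, a briefing for the staff who apply the labels, and invitations to a visit already planned. Nothing here changes when or why a participant stops exercising; it settles only whether that person is still measured and how they are analysed.
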